### Who will be included in each analysis {27b}

All analyses are performed in the intention-to-treat (ITT) population.

### How missing data will be handled in the analysis {27c}

Missing values are treated as missing at random and replaced using maximum likelihood estimation within the mixed-model analyses. We will perform the following sensitivity analyses to handle missing data: We will test for systematic study or treatment dropout in both intervention groups regarding the primary outcome at the beginning of treatment as well as age, gender, time since diagnosis and occurrence of illness progression within the last three months (time-dependent covariate). In case of systematic dropout, we will perform sensitivity analyses using multiple imputation to replace missing values due to dropout based on the existing data of similar participants. Because of the seriously ill study population, we expect some dropouts and resulting missing values due to death or physical inability to complete the assessments. We will perform sensitivity analyses by excluding these participants from our analyses.

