### Plans to promote participant retention and complete follow-up {25b}

Each ORPHYS and TAU session will be documented on a structured, standardized form including date and time of the session, setting (e.g., face-to-face, telephone, home visit), attendance, occurrence and severity of adverse events, and study or treatment dropout. If patients miss an appointment without canceling in advance, therapists will contact them via phone and document reasons for cancellation and the next planned appointment. If participants do not return the self-report questionnaires within 14 days, study personnel will remind them via telephone.

We document information relevant to the data collection process (e.g., dates of follow-up assessments, return of self-report questionnaires, dropout). If participants discontinue or deviate from intervention protocols, study personnel will document reasons for study or treatment dropout. Outcome data that are collected before dropout will be included in the analyses.

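### The missing-data sensitivity analyses fixed in section 27c do not probe missing-at-random: one stays within it and runs only on a trigger, the other drops patients lost to death or physical inability

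*Protocol article*

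**What the plan says.** All references are to the protocol article.

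- **Primary assumption (section 27c).** "Missing values are treated as missing at random and replaced using maximum likelihood estimation within the mixed-model analyses".
- **Trigger (27c).** "We will test for systematic study or treatment dropout in both intervention groups regarding the primary outcome at the beginning of treatment". The variables listed next are age, gender, time since diagnosis and recent illness progression.
- **First sensitivity analysis (27c).** "In case of systematic dropout, we will perform sensitivity analyses using multiple imputation to replace missing values due to dropout". The replacement values are "based on the existing data of similar participants".
- **Second sensitivity analysis (27c).** The authors write that "we expect some dropouts and resulting missing values due to death or physical inability to complete the assessments", and then: "We will perform sensitivity analyses by excluding these participants from our analyses".
- **Further sensitivity analyses (27d).** The linear mixed model is refitted with age, gender, time since first diagnosis and time since diagnosis of incurable disease. It is also adjusted for progression in the last 3 months as a time-dependent covariate.
- **Population (27b).** "All analyses are performed in the intention-to-treat (ITT) population".
- **Data before dropout (25b).** "Outcome data that are collected before dropout will be included in the analyses".
- **Expected loss (section 19).** Completion is put at 80%, and the shortfall is ascribed to death or physical deterioration.

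**The concern.** A sensitivity analysis for missing data should vary the assumption that the data cannot check. Here that assumption is that patients without a 6-month score would, given their observed data, have scored like those who have one. The plan itself expects the losses to come from death and deterioration, which may well go with demoralization beyond what earlier scores show. If every analysis in the article stays within MAR, or simply leaves the affected patients out, the results could agree with each other and share the same bias.

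The second analysis also treats two different problems as one. After death there is no later score to estimate. A patient too ill to complete the questionnaire has a score that was not observed. One exclusion rule answers neither question.

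**Working it through.** **1. The plan's own figures.** For d = 0.5, two-sided alpha 0.05 and 80% power, the noncentral t solution is 63.77, so 64 per arm and 128 in total. Allowing for 20% loss, 128 / 0.80 = 160. Both figures in section 19 reproduce. Planned loss is 160 x 0.20 = 32 patients, or 16 per arm.

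**2. Which assumption each analysis varies.**

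| Analysis | Assumption about unseen scores | Probes MAR? |
|---|---|---|
| Primary mixed model (27a, 27c) | MAR given the model | – |
| Imputation from similar participants (27c) | MAR given more variables; no shift or reference term named | No |
| Covariate-adjusted models (27d) | MAR given the added covariates | No |
| Exclusion of patients lost to death or inability (27c) | None; patients removed | No |

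**3. The trigger.** The test compares dropout across observed variables. A positive result is compatible with MAR, because MAR allows loss to depend on observed data. A null result says nothing about dependence on the unseen score. The trigger therefore does not bear on the assumption, and it makes the analysis depend on the data. No threshold is given.

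**4. The exclusion against the other sections.** Section 27b places all analyses in the ITT population, and 25b keeps outcome data collected before dropout. The exclusion removes participants rather than visits, so the earlier scores of up to 32 of 160 patients go too.

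**5. What exclusion does even when MAR holds.** This was a simulation on assumed inputs: 200,000 per arm, SD 5.4, true 6-month effect -2.7 (half of it at 3 months), 20% lost per arm before month 6, and loss depending on the observed 3-month score. The 3-to-6-month correlation was 0.4, 0.6 or 0.8.

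| Loss depends on 3-month score | Exclusion | All data used |
|---|---|---|
| Same way in both arms | -2.69 to -2.71 | -2.69 to -2.71 |
| High scorers lost, TAU only | -1.98 to -2.32 | -2.70 to -2.72 |
| High scorers lost, ORPHYS only | -3.11 to -3.46 | -2.70 to -2.73 |
| High scorers lost in ORPHYS, low scorers in TAU | -3.47 to -4.23 | -2.69 to -2.73 |

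Exclusion can move the estimate either way while the primary assumption is true. A difference from the primary result would therefore not show that MAR failed.

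**6. What a departure from MAR would do.** Let delta be the number of points by which unseen 6-month scores are worse than the model predicts. The shift in the contrast is

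shift = (fraction missing in ORPHYS x delta in ORPHYS) - (fraction missing in TAU x delta in TAU).

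Assume 20% missing in each arm, all treated as non-death, and a penalty in ORPHYS only:

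- delta = 1 point: 0.2 x 1 = 0.2
- delta = 0.5 SD = 2.7 points: 0.2 x 2.7 = 0.54
- delta = 1 SD = 5.4 points: 0.2 x 5.4 = 1.08

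Section 19 calls a 2-point difference clinically relevant, so 0.54 is 27% of it and 1.08 is 54%. Equal deltas and equal loss in both arms cancel.

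**7. Tipping points.** With 64 per arm, SE = 5.4 x sqrt(2/64) = 0.955, and the smallest significant difference is 1.89. This ignores both the information in earlier scores and the imputation variance.

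- Observed effect 2.7 (d = 0.5 at SD 5.4): (2.7 - 1.89) / 0.2 = about 4.1 points.
- Observed effect 2.0 (the stated relevant difference): (2.0 - 1.889) / 0.2 = about 0.55 points.

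None of the analyses named in the article would show either.

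**The case against.** The strongest reply is that the statistical analysis plan is not shown. Section 5 promises it before data lock, and it could add a not-at-random analysis. That stands, so the article cannot be faulted for lacking one. It does not rescue the two analyses that section 27c already fixes.

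Four further points also stand in whole or part.

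- **ITT.** A reader might infer that the trial's ITT analysis is broken. It is not. The primary model keeps all randomized patients and their earlier data, and the exclusion is labelled a sensitivity analysis. The conflict is with the wording of 27b and 25b.
- **Redundancy.** A reader might call the imputation a repeat of the primary model. The primary model has no prognostic covariates, so MAR given age, gender, time since diagnosis and progression is a different and usually weaker assumption. The estimate could move. The adjustment for progression in 27d likewise addresses deterioration, as far as it is observed. Both remain within MAR.
- **Size.** A reader might take 1.08 points as the bias of the primary analysis. It is not. The mixed model already uses earlier scores, so only the part of the gap they do not predict remains. The documents give no value for delta and no evidence that it differs by arm.
- **Direction.** Exclusion was about unbiased when loss worked alike in both arms. Bias needs a differential mechanism. That is plausible with unblinded arms and different session intensity, but it is an assumption.

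Finally, 27c says only that dropout will be tested. A formal significance test is the natural reading, but it is not stated.

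**Conclusion.** The point holds in a limited form. The missing-data sensitivity analyses that section 27c fixes, together with the adjusted models in 27d, leave MAR unexamined, although section 19 ascribes the whole planned 20% loss to death or deterioration. The trigger is uninformative about MAR. The exclusion selects on post-randomization events, discards observed scores, merges death with unobserved outcomes, and contradicts the wording of 27b and 25b.

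The possible shift is 0.2 points in the contrast per point of delta, on the assumptions of 20% missing per arm, no deaths among them and a penalty in ORPHYS only. The 0.54-point case is moderate and the 1.08-point case is at the upper end. The confirmatory test itself is unchanged. What is at stake is whether its robustness can be judged.

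**What to change.** 1. Remove the condition on systematic dropout. Whatever any test shows, run multiple imputation in all randomized patients with an arm-specific delta for missing values not due to death, and increase delta until the conclusion changes.
2. Handle death separately, in a pre-specified analysis that keeps all randomized patients. The method is for the trial statistician to choose. Worst-rank is one option, but it changes the quantity being estimated.
3. Delete the exclusion analysis, or relabel it as a supplementary survivor or completer description and exempt it from the ITT statement in 27b and the retention statement in 25b.

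Dates of death and reasons for dropout are already collected, so no new data are needed. The cost is revised wording in the protocol and the analysis plan, and a little more analysis work.

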### Methods for additional analyses (e.g., subgroup analyses) {27d}

#### Sensitivity analyses

We will perform sensitivity analyses by including the covariates age, gender, the time since first diagnosis, and the time since diagnosis of incurable cancer in the linear mixed model based on their association with the primary outcome demoralization in previous studies [9, 13]. Moreover, we will adjust the model for the occurrence of illness progression within the last 3 months by including a binary time-dependent covariate.

### Interim analyses {28b}

We will not perform interim analyses.

### Protocol and statistical analysis plan {5}

We will submit the statistical analysis plan as a supplement under “Study Documents” on ClinicalTrials.gov before data lock.

## Oversight and monitoring

### Composition of the coordinating center and trial steering committee {3d}

Study personnel of the 3 trial sites as well as the Institute of Medical Biometry and Epidemiology are committed to ethical standards and the Guidelines for Safeguarding Good Research Practice by the German Research Foundation [98]. They meet once a month to discuss the recruitment process (e.g., recruitment goals, dropout), data collection and data management (e.g., missing data). Meetings will be organized by the study personnel in Hamburg (coordinating trial site) and led by the principal investigator (SV). ORPHYS therapists participate in group supervision once a month. Supervision will be organized by the principal investigator (SV) and led by two external licensed psychotherapists.

### Composition of the data monitoring committee, its role and reporting structure {28a}

A data-monitoring board, consisting of independent researchers with clinical and statistical expertise as well as expertise in the conduct of related clinical trials, will enable detection of potential adverse events (AE) early on and take appropriate measures due to close monitoring (documentation of therapy sessions, process variables) and supervision, thus minimizing the risk of serious AEs (SAE, suicidality, suicide). If the AE is treatment-related, it is characterized and documented as an adverse treatment reaction (ATR). Serious ATRs (death, life-threatening conditions, need for hospitalization) are reported immediately to the ethics committee. In case of suicidality, therapists are trained to follow a detailed standard operating procedure "suicidality" [88]. They will further contact the principal investigator and responsible local study manager immediately. Study personnel will discuss mild to moderate AEs (e.g., distress during the interviews) with patients and together they will decide on appropriate measures. If participants discontinue the trial or intervention, we document their reasons (e.g., study or treatment dropout due to an ATR) and assess consent or withdrawal from further assessments.

### Frequency and plans for auditing trial conduct {29}

The trial conduct, including participant safety and trial integrity, is monitored by an independent expert, who will audit 10% of all study files every 6 months throughout the course of the study.

### Protocol amendments {31}

Changes to the protocol will be reported in the study registration (https://clinicaltrials.gov/study/NCT07312760).

## Dissemination policy {8}

Dissemination of study results includes the following strategies: publication in peer-reviewed open-access journals, conference presentations, and executive summaries (e.g., for participants, for the funding institution).

## Discussion

The challenge for advanced-cancer patients to psychologically adapt to the profound changes and numerous losses caused by their illness has become a key issue in psycho-oncological research. While every fifth patient suffers from high existential distress and comorbid mental disorders, the number of patients struggling to process the psychological challenges of living with a serious physical illness may increase, as advances in cancer treatments lead to extended survival. Clinicians face difficulties in treating vulnerable patients, who feel overwhelmed by existential fear and avoid engaging in end-of-life conversations that touch emotional conflicts between attachment and loss of shared time, the need to be cared for and loss of autonomy, or self-worth and fears of rejection. We developed ORPHYS in line with current research on psychodynamic interventions and treatment techniques that have been described as helpful in alleviating cancer patients’ existential distress by strengthening patients’ capacity to process intense emotions through establishing a holding and containing therapeutic alliance (ClinicalTrials.gov NCT05520281; [34]).

In this RCT, we address the lack of systematic evidence for the efficacy of psychodynamic psychotherapies in highly distressed and seriously ill cancer patients, who may benefit from regular therapy sessions over a longer period of time to limit the risk of feeling overwhelming despair when touching on existential issues. Compared to previous trials [99, 100], we investigate the effect of psychodynamic psychotherapy on a reduction of symptoms of demoralization, because we hypothesize this outcome to sensitively reflect potential changes due to treatment by taking into account the aim of psychodynamic approaches to increase patients’ capacity to integrate conflicting mental states [101].

We expect that potential methodological limitations will be due to physical deterioration or death in this vulnerable population leading to lower response rates for long-term follow-up assessments, higher treatment dropout rates, and a more challenging acquisition of the pre-specified treatment dosage (e.g., due to interruptions of treatment associated with hospital admissions or rehabilitation).

Results of this RCT will contribute to our knowledge about the benefits of short-term psychodynamic psychotherapy in targeting patients’ existential distress arising from emotional conflicts that are associated with cancer and prolonged survival. Data for the effect of ORPHYS as compared to standard treatment in mitigating patients’ distress will inform clinicians on how to best support patients who struggle with engaging in end-of-life conversations.

## Trial status

This trial is at protocol version 3, dated February 6th, 2026. Date of first enrollment: October 24th, 2025. Recruitment will be completed in December 2027. The study’s clinical trial registration numbers are DRKS00038173 registered with https://www.drks.de/search/de and NCT07312760 registered with https://clinicaltrials.gov/.

## Data Availability

No datasets were generated or analysed during the current study.

## Abbreviations

AE: Adverse event
SAE: Serious adverse event
ATR: Adverse treatment reaction
ITT: Intention-to-treat
ORPHYS: Short-term psychodynamic psychotherapy in serious physical illness
PP: Per-protocol
RCT: Randomized controlled trial
TAU: Usual psycho-oncological treatment
UICC: Union Internationale Contre le Cancer
